**Fig. 1 Fig1:**
[figure not shown]
Flow chart of the study

All data will be encrypted and identifiable only by a code not linked to the participant’s identity. The only real-time interaction with staff will be during scheduled telephone diagnostic interviews at pre-, post-, and follow-up assessments. No spontaneous calls will be made unless safety concerns arise, such as severe suicidal intentions reported by a participant. If the participant is assessed as high risk at the time of the screening, the person concerned will not be admitted to the study and we will (a) explain to them why they are excluded from the study, (b) ask them to provide us the contact information of a close person, and (c) also provide them the list of therapists as well as phone numbers of all psychiatric emergencies in all French-speaking cantons and of our internal centers as well as of Centre Psychosocial of the Réseau fribourgeois de santé mentale (RFSM) in Fribourg. If they withdraw from the study, the data collected up to this point will be used for further analysis since it is important for the study’s scientific value. Also, for each included participant, we will elaborate with them an individualized safety plan after they have been included for the case their symptoms worsen during the course of the study. The safety plan will include the fact that 1) they should inform us if this happens, which persons or professional help should be contacted, and that they also can get support from the study team on the phone.

Adherence strategy: To encourage study adherence, participants will receive compensation at various stages of the study. While there is no direct compensation for engaging with the Deprexis program, participants will receive the monetary rewards earned during the Fribourg reward task at T0 and T2 (maximum CHF 24) and an additional CHF 10 for completing the questionnaires at each time point (T0, T1, T2), for a total of CHF 30. To further support participation, psychology students at the University in Switzerland can opt to receive experimental credits instead of monetary compensation (2 credits per time point, up to a maximum of 6 credits). By offering structured financial incentives and academic credits, the study aims to enhance adherence by maintaining participants’ engagement and ensuring completion of all study phases.

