### Participants

Participants will be recruited through flyers and emails, word-of-mouth, social media (e.g., Facebook, Instagram), depression-related websites, private psychotherapists, outpatient clinics in French-speaking Switzerland, and the English-speaking population from India. Interested participants will receive information on the study, and then they will be given at least 24 h to confirm their participation by signing and returning the informed consent of the study (via email). They will be screened to assess eligibility using a rapid eligibility check, using the inclusion and exclusion checklist and the Patient Health Questionnaire (PHQ-9; [57]).

The inclusion criteria are (1) providing signed informed consent; (2) being at least 18 years of age; (3) having access to a computer/laptop/tablet/smartphone with an internet connection; (4) having sufficient French language skills in Switzerland and English in India; (5) meeting criteria for mild to moderate depression as operationalized by the Patient Health Questionnaire-9 (PHQ-9 = 5–14) (PHQ-9; [57]) meeting the diagnostic criteria of the characterized depressive disorder according to the diagnostic interview by telephone; and (7) providing the emergency contact before treatment.

However, they will be excluded from the study if they present any of the following criteria: (1) having active suicidal plans (if they have a score of 2 or higher on the suicide item of the PHQ-9 [57] or with active suicidal plans in the diagnostic telephone interview; (2) having a history of psychotic disorder or bipolar disorder; and (3) changing their dosage of prescribed medication for anxiety or depression in the last month before the study. When potential participants fulfill inclusion criteria, they will be interviewed by telephone for screening using the MINI International Neuropsychiatric Interview (M.I.N.I; [58]). The current protocol is prepared in accordance with the “Standard Protocol Items: Recommendations for Interventional Trials (SPIRIT) 2013” guidelines [59].

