### Procedure

This study will be entirely online. All participants will undergo the same screening procedure, including a standardized questionnaire (PHQ-9; [57]) and a structured clinical psychiatric interview (MINI; [58]) performed via telephone. Assessments will be performed by trained research assistants from the University and supervised by a clinician from our department. Eligible participants will be randomized into one of three groups of 80 participants each: one with Deprexis only, one with Deprexis and peer-to-peer support online forum, and a control group on a waiting list, which will access Deprexis after 8 weeks.

The first group will use Deprexis, an internet-based self-help treatment based on cognitive-behavioral therapy, for 8 weeks. The second group will have access to Deprexis and a peer-to-peer support forum for sharing and support. The third control group will access Deprexis after the initial 8 weeks. Measurements will be taken at baseline (T0), mid-intervention (4 weeks, T1), post-intervention (8 weeks, T2), and follow-up (3 months after intervention, T3) (see Table 1). Participants will complete online questionnaires on RedCap (https://redcap.unifr.ch) and an adapted online version of the Fribourg reward task [46–48] at different study points (see Fig. 1).

**Table 1 Tab1:** This table demonstrates different psychometric measures used in the study

Study Periods	Screening	Baseline measures (T0)	Mid-intervention (T1)	Post-intervention (T2)	Follow-up (T3)	“End-of-study” visit
Visit	1	2	3	4	5	6
Time (weeks/day)	−2 weeks- 0	0	+ 4 weeks ± 2 weeks	+ 8 weeks ± 2 weeks	+ 20 weeks ± 2 weeks	Any time after completion or withdrawal
Patient information sheet	x					
Informed consent (after at least 24 h)	x					
PHQ-9 (including suicidal risks)	x	x	x	x	x	
MINI	x					
In-/exclusion criteria checklist	x					
SHAPS		x	x	x	x	
BIS/BAS		x	x	x	x	
MSPSS		x	x	x	x	
GAD-7		x	x	x	x	
SF-12		x	x	x	x	
RSES		x	x	x	x	
GSES		x	x	x	x	
PSS		x	x	x	x	
SSS-8		x	x	x	x	
PCL-5		x	x	x	x	
CTQ-SF		x	x	x	x	
SUS				x		
CSQ			x	x		
NEP			x	x	x	
Fribourg Reward Task		x	x	x		

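### High-risk screenees in both countries get the same response, but its only located emergency numbers and its only named service are in French-speaking Switzerland, although the trial also recruits in India

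*Protocol article*

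**What the plan says.** The Participants section describes recruitment through several channels, including "outpatient clinics in French-speaking Switzerland, and the English-speaking population from India". The Procedure section makes the study entirely online and states that "All participants will undergo the same screening procedure": the PHQ-9, then a structured psychiatric interview by telephone.

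The text after Fig. 1, still under Procedure, sets the response to high risk: "If the participant is assessed as high risk at the time of the screening, the person concerned will not be admitted to the study". The team then (a) explains the exclusion, (b) will "ask them to provide us the contact information of a close person", and (c) hands over a list of therapists, "phone numbers of all psychiatric emergencies in all French-speaking cantons", and the numbers of its internal centres and of the "Centre Psychosocial of the Réseau fribourgeois de santé mentale (RFSM) in Fribourg".

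The same paragraph adds that "for each included participant, we will elaborate with them an individualized safety plan".

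**The concern.** The response has no country restriction, but the resources in step (c) that have a stated location are all in French-speaking Switzerland. The article does adapt to country elsewhere: the language criterion under Participants and the questionnaire versions under Study outcome measures both distinguish Switzerland from India. Step (c) makes no such distinction.

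The people concerned are identified remotely and are sent away from the study at that moment. High risk is not defined where the step is described. The nearest stated criterion is the exclusion for "having active suicidal plans (if they have a score of 2 or higher on the suicide item of the PHQ-9", or active suicidal plans found at the telephone interview. For such a person, a crisis number that works where they live is the most immediate help the team can give. What is at stake is participant safety in one of the two recruiting countries, not inference.

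**Working it through.** No arithmetic applies. The check sets the relevant statements of the protocol article side by side.

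**Who can reach the step**

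- Recruitment covers French-speaking Switzerland and English-speaking people in India (Participants).
- Screening is the same for all and is done remotely (Procedure).
- The suicidality exclusion and the high-risk response carry no country qualifier (Participants; Procedure, after Fig. 1).

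A screenee in India can therefore be assessed as high risk and enter this step.

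**What such a person receives**

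| Item | Stated location | What it gives a high-risk screenee in India |
|---|---|---|
| (a) Explanation of the exclusion | Not applicable | Information only |
| (b) Request for a close person's contact details | None; applies in both countries | A local route for the team, but no number for the person |
| (c) List of therapists | Not stated | Possibly Indian therapists; listed separately from the emergency numbers |
| (c) Psychiatric emergency numbers | French-speaking cantons | Numbers for another country |
| (c) Internal centres | Not stated; Swiss by context, which is an inference | Nothing stated to serve India |
| (c) Named centre | Fribourg | A service in another country |

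**Whether another provision fills the gap**

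- The individualised safety plan is made with included participants, after inclusion. A person excluded at screening does not get one.
- The emergency contact under Participants is an inclusion criterion, to be supplied before treatment. It is not a resource handed to people who are excluded.
- The Data Safety Monitoring Committee section describes internal monitoring at the department and adds no local crisis route.
- The Limitation section has nothing on crisis contacts.

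No Indian emergency number, helpline or referral service is mentioned anywhere in the article.

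**How many people**

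The Trial status section reports 28 recruited as of August 2025, without a country breakdown, and the article gives no high-risk rate at screening. The number affected cannot be derived. Against the planned 240, 240 − 28 = 212 participants were still to be recruited at that date, with recruitment expected to run to May 2026. Most screening therefore still lay ahead, although the article does not say how much of it would be in India.

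**The case against.** The strongest reply is that a journal article condenses. An ethics-approved protocol (version 4, dated 22.05.2024) and supplementary material exist and are not shown, and country-specific contact lists are operational content that an article may leave to them. The Swiss list could be a shortened example. This stands in part: the article alone cannot show whether Indian contacts exist elsewhere. It does not remove the point, because the article is not silent here. It itemises the resources down to the cantons and one named centre, and it neither defers to another document nor says that the list is adapted by country.

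Two items in step (c), the therapist list and the internal centres, have no stated location, so it cannot be said that every resource is Swiss. That is correct. It remains true that none is stated to be a crisis contact valid in India.

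There are also mitigating safeguards. Research assistants carry out the assessments under a clinician's supervision, unscheduled calls are allowed when safety concerns arise, and a close person's contact is requested in both countries. These reduce the risk. However, the PHQ-9 eligibility check precedes the interview, so someone excluded on the suicide item may never reach the supervised telephone call, and the provision for unscheduled calls may be meant for enrolled participants. None of these safeguards supplies a local crisis number.

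Finally, the point touches no estimand, outcome or test. That is so; it is a participant-safety point about how the step is designed.

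**Conclusion.** The concern holds. Read as written, the high-risk step applies in both countries, while its only located emergency numbers and its only named service are in French-speaking Switzerland. An excluded high-risk screenee in India leaves with no crisis number stated to work there, and no other provision in the article supplies one.

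The gap is confined to high-risk screenees in India, and its size cannot be stated. The conclusion assumes that the article describes the step as it is carried out. If the full protocol already contains Indian contacts, the fault is only in the article's wording. For that reason confidence is medium, and this is a change that should be made rather than a defect that invalidates the trial.

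**What to change.** Amend step (c) so that every screenee assessed as high risk receives emergency numbers and a therapist or referral list valid in their own country, and add the Indian entries. If the full protocol already has them, confirm this and state that the list is adapted by country. Do this before screening in India proceeds. The choice of numbers and services belongs to the clinical team.

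The cost is one sentence and a locally valid contact list. Sample size, randomisation and analysis are unaffected.

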### Study outcome measures

All outcome measures will be assessed online with validated French versions (for Swiss participants) and English versions (for Indian participants) of the original questionnaires.

#### Primary outcome measures

Patient Health Questionnaire (PHQ-9; English version [62]; French version [57]). This self-reported measure is used in several RCT studies to assess depressive symptoms [34, 36]. The PHQ-9 is a valid, reliable, and useful tool for clinical and research purposes.

#### Secondary outcome measures

##### Fribourg reward task

In parallel, participants will be asked to complete an online reward task, to measure reaction times, accuracy, and mood reactions to both monetary and social rewards. For this, we will use an online adapted behavioral version of the Fribourg reward task [46–48]. This task was originally programmed using E-Prime software (version 1.1.3, Psychology Software Tools Inc., Pittsburg, Pa., USA) and made available online using OpenSesame, a graphical experiment builder for the social sciences. The experimental task was presented in three block conditions, comprising reward conditions (monetary reward, social reward, and no reward). For this task, there are three conditions (monetary reward, social reward, and no reward). Each condition consists of 12 trials, and the order of the blocks was pseudo-randomized. In the three-reward conditions, at the onset of each trial, a visual cue (2000 ms) was presented (3 yellow circles), along with the reward associated with performance. After the presentation of a fixation cross (500 ms), participants saw an array of yellow circles (3 circles, 2000 ms). A fixation cross (3000 ms) was presented before the visual target. The visual target (a green circle, 3000 ms) was displayed in any position on the screen and signaled that the participant should decide as quickly as possible whether this circle was in the same position as one of the circles presented previously. After response execution and a variable jittered interstimulus interval (ISI; 0 ms or 2000 ms), the feedback screen (1500 ms) informed the participant of their winnings. In each condition, the way correct and incorrect trials are presented differs as follows:In the social reward condition: a neutral face is presented for incorrect trials and a smiling face for correct trials.In the monetary reward condition: a screen with “CHF 0” is shown for incorrect trials and “CHF 1” for correct ones.In the control condition: a blank screen is presented in both correct and incorrect trials.

At the end of all trials, a feedback screen (1000 ms) indicating the cumulative amount of monetary reward or social reward (smileys) earned (in the monetary and social reward conditions) or a blank screen in the no-reward condition was presented. Correct responses were associated with monetary gains (“CHF 10”) in the monetary reward condition. Correct responses were not associated with any gains in the no-reward condition. We asked participants to rate their momentary mood and stress level using a visual analog scale from 0 (bad mood)—10 (good mood), with smileys at the anchor points (0 =; (10 =). Participants rated their momentary mood and stress level on a scale of 0 to 10 at baseline, at the beginning of the experimental session, and before and after each block for a maximal duration of the 20 s. Participants were informed that they would receive the total sum in cash at the end of the session. Participants underwent a training phase before proceeding to the main task. A criterion of 70% correct responses was chosen to prevent arbitrary guessing and thereby verify understanding of the task and ensure that participants would win similar amounts of money.

Snaith-Hamilton Pleasure Scale (SHAPS; English version [63, 64]; French version [63]). The SHAPS measures the ability to experience pleasure. It covers four different areas of hedonic experience: interest/pastimes, social interaction, sensory experience, and food/drink. The scale has good internal consistency in both English and French and correlates significantly with other measures of effect and personality [62, 63].

Behavioral Inhibition System/Behavioral Activation System (BIS/BAS; English version [65]; French version [66]). This scale is a self-reported questionnaire, which measures two aspects linked to personality, that is the activation and the inhibition systems, or sensitivity to punishment and reward. The BIS/BAS scales show good internal consistency in both subscales [67].

Perceived Social Support (MSPSS; English version [68]; French version [69]). The PSS is a self-report questionnaire, which assesses the perception of support from family, friends, and a significant other. The PSS scale shows good psychometric properties with good internal consistency in both English and French [67, 68].

#### Moderators and mediators

Generalized Anxiety Disorder Scale (GAD-7; English version [70]; French version [71]). The GAD-7 measures general anxiety symptoms, such as feeling nervous, worried, having trouble relaxing, restlessness, feeling annoyed or irritable, and feeling afraid that something awful might happen. Internal consistency of the GAD-7 is good in both the original and French versions, and it has good convergent validity with other anxiety scales [72].

Short-Form Health Survey-12 (SF-12; English version [73]; French version [74]). Quality of life is assessed with the SF-12. Two subscales measure respectively physical and mental aspects of health-related quality of life. The SF-12 shows good psychometric properties, roughly equivalent to the long form, the SF-36, and is widely used as an estimate of the general quality of life [72].

Rosenberg Self-Esteem Scale (RSES; English version [75]; French version [76]). The RSE scale is a self-report scale that measures one’s overall sense of worthiness as a person and has been translated and used worldwide, indicating that self-esteem is a global measure across cultures [77].

General Self-Efficacy Scale (GSES; English version [78]; English version [79]). This trait scale assesses the belief in one’s competence to cope with challenging demands. Its internal consistency is good and has been shown to be a universal construct across 25 countries [77, 78].

Perceived Stress Scale-Short Version (PSS; English version [80]; French version [81]). The PSS scale is a widely used psychological instrument to measure perceptions of stress. It is a self-reported questionnaire. The internal consistency of the scale is good in both French and English [79].

Somatic Symptom Scale (English version [82]; French version [83]). This scale is a brief self-report questionnaire used to assess somatic symptom burden. It measures the perceived burden of common somatic symptoms. The internal consistency of the scale is good in both French and English [82].

Post-Traumatic Stress Disorder Checklist for DSM-5 (PCL-5, English version [84]; French version [85]). The PCL-5 is a 20-item questionnaire, corresponding to the DSM-5 symptom criteria for PTSD. The scale ranges from 0 to 4 for each symptom from “Not at all,” “A little bit,” “Moderately,” “Quite a bit,” and “Extremely.” The PCL-5 shows good psychometric properties and is widely used as an estimate of the general quality of life [83].

Childhood Trauma Questionnaire-Short Form (CTQ-SF; English version [86]; French version [87]). The CTQ-SF is a retrospective, self-report measure that was developed to provide a brief, reliable, and valid assessment of a broad range of traumatic experiences in childhood. It assesses experiences of abuse and neglect in childhood, including physical, emotional, and sexual abuse and physical and emotional neglect, as well as related aspects of the child-rearing environment. The CTQ-SF is intended for adolescents and adults. It contains 5 items arranged according to four factors: physical and emotional abuse, emotional neglect, sexual abuse, and physical neglect. Responses are quantified on a 5-point Likert-type scale according to the frequency with which experiences occurred, with 1 = “never true” and 5 = “very often true.” The CTQ has good psychometric properties which make it a reliable and valid measure for assessing CTQ’s in English and French-speaking populations, both for research purposes and clinical practice [88].

#### Treatment characteristics

System usability scale (SUS; English version [89]; French version [90]). The SUS allows the evaluation of the user experience and the satisfaction related to the use of a product. This scale has been widely used since the beginning [91]. The scale presents a good internal consistency [88, 89].

Client Satisfaction Questionnaire (CSQ; English version [92]; French version [93]). The CSQ-8 is a self-report questionnaire that assesses the general level of satisfaction with the service received. It was originally developed to measure satisfaction with inpatient treatment. In this study, we will use a version that was slightly adapted for internet-based treatments, and that has shown good internal consistency in previous studies [33, 94].

Negative Effects of Psychotherapy (NEP; [95]). This is a tool used to assess and measure various negative occurrences or consequences that can arise from psychological interventions or treatments. The primary purpose of the scale is to systematically evaluate and quantify adverse outcomes that may result from receiving psychological treatment. The scale covers a broad spectrum of potential negative incidents, such as intensification of symptoms, unintended side effects of treatment, client dissatisfaction or disillusionment, therapist-client relationship strains, miscommunication or misunderstandings, ethical concerns or breaches. Items on the scale are typically developed through empirical research and clinical observations to ensure they adequately capture the diverse array of negative incidents that could occur during or as a result of psychological treatment [94].

